## Abstract

**Background:**

There is a large treatment gap with few community services for people with schizophrenia in low income countries largely due to the shortage of specialist mental healthcare human resources. Community based rehabilitation (CBR), involving lay health workers, has been shown to be feasible, acceptable and more effective than routine care for people with schizophrenia in observational studies. The aim of this study is to evaluate whether a lay health worker led, Collaborative Community Based Care (CCBC) intervention, combined with usual Facility Based Care (FBC), is superior to FBC alone in improving outcomes for people with schizophrenia and their caregivers in India.

**Methods/Design:**

This trial is a multi-site, parallel group randomised controlled trial design in India.

The trial will be conducted concurrently at three sites in India where persons with schizophrenia will be screened for eligibility and recruited after providing informed consent. Trial participants will be randomly allocated in a 2:1 ratio to the CCBC+FBC and FBC arms respectively using an allocation sequence pre-prepared through the use of permuted blocks, stratified within site. The structured CCBC intervention will be delivered by trained lay community health workers (CHWs) working together with the treating Psychiatrist. We aim to recruit 282 persons with schizophrenia. The primary outcomes are reduction in severity of symptoms of schizophrenia and disability at 12 months. The study will be conducted according to good ethical practice, data analysis and reporting guidelines.

**Discussion:**

If the additional CCBC intervention delivered by front line CHWs is demonstrated to be effective and cost-effective in comparison to usually available care, this intervention can be scaled up to expand coverage and improve outcomes for persons with schizophrenia and their caregivers in low income countries.

**Trial registration:**

The trial is registered with the International Society for the Registration of Clinical Trials and the allocated unique ID number is ISRCTN 56877013.

## Background

Schizophrenia is a severe mental disorder that usually has an onset in early adulthood and is often associated with persistent or relapsing symptoms and a range of other adverse outcomes [1,2]. Even though a low prevalence disorder, schizophrenia contributes an estimated 1.1% of the total Disability Adjusted Life Years (DALY's) and 9.5% of the total DALY's attributable to the neuropsychiatric disorders [3] in South East Asia making it a priority public health concern for the region. There is international consensus that care for people with schizophrenia should largely be delivered in community settings for the best outcomes[4]. While in high resource countries, community care is the norm, in low income countries, the availability of community services is the exception[5]. Thus, for the majority of persons with schizophrenia and their caregivers in low income countries, including in India, there is little access to any care [6]. Addressing this 'treatment gap' by scaling up accessible, acceptable and effective community based services for persons with schizophrenia is an urgent public health and ethical priority in countries like India[7].

Scaling up of community services in low income countries faces challenges like the paucity of specialist resources and the lack of evidence around the effectiveness, costs and processes involved in delivering community based interventions. One method that specifically addresses the challenges of the lack of specialist resources, accessibility and inequity in care provision is the Community Based Rehabilitation (CBR) strategy for persons with disabilities- a health and social intervention that is largely implemented by appropriately trained, lay persons within community settings[8]. In addition, the CBR method has a strong focus on empowerment of service users, social inclusion, livelihood support and equalising of opportunities for people with disabilities; all of these are of particular relevance to persons with schizophrenia. A non-randomised controlled study from rural India showed that CBR using trained lay community workers was feasible and improved outcomes for people with schizophrenia, compared with routine outpatient care [9]. A more recent study from the same site has described the impact of specific components of the complex intervention on long-term outcomes in people with schizophrenia[10]. These encouraging results need to be rigorously tested through a randomized controlled trial. If demonstrated to be clinically effective and affordable in comparison to usually available care (i.e. facility based care) alone, such interventions can be scaled up expand coverage and improve outcomes of persons with schizophrenia and their caregivers in low income countries by using available and low cost human resources.

### Objectives

The objectives of the trial are: firstly, to test the hypotheses that usual, Facility-Based Care (FBC), when combined with a Collaborative Community-Based Care intervention (CCBC), will be superior to Facility-Based Care alone in improving a range of outcomes in people with schizophrenia and their caregivers and, secondly, to determine if the CCBC intervention is cost effective in India.

The primary objectives of the trial are to determine whether the FBC+CCBC intervention will be superior to FBC alone in:

i) reducing symptoms of schizophrenia at 12 months, and

ii) reducing disability related to schizophrenia over 12 months.

In *persons with schizophrenia*, the secondary objectives are to determine whether, FBC+CCBC will be more effective than FBC alone, in:

• improving adherence to antipsychotic treatment

• reducing experiences of stigma and discrimination

For *caregivers of people with schizophrenia*, the secondary objectives are to determine

whether, FBC+ CCBC will be superior to FBC alone, in:

• improving their knowledge and attitudes about the illness

• reducing their burden of caring

• reducing experiences of stigma and discrimination.

The health economic objective is to compare the costs and assess the cost-effectiveness and cost-utility of the FBC+ CCBC intervention compared to FBC alone.

The COPSI trial is a collaborative effort between multiple institutions and individual Psychiatrists at the Indian sites. The lead institution is the Institute of Psychiatry (IoP), Kings' College, London, while the partner organizations are the London School of Hygiene and Tropical Medicine (LSHTM), Sangath in Goa, the Schizophrenia Research Foundation (SCARF) in Chennai, the National Institute of Mental Health and Neuroscience (NIMHANS) in Bangalore and Parivartan and Nirmittee in Satara. In Goa and in Satara, the individual collaborators are Psychiatrists working in the private sector.

## Methods/Design

### Study design

Effectiveness, parallel group, randomised controlled trial design with unequal allocation of participants between arms. The two arms of the study (allocation ration 2:1) will compare people with schizophrenia allocated to receive: (i) FBC+ CCBC, or (ii) FBC only, with follow up over 12 months.

### Setting

The trial will be conducted in three sites in India- in four rural blocks or sub-districts in the southern Indian state of Tamil Nadu and in two sites in western India, - across the state of Goa and in Satara in the state of Maharashtra. The relevant details of the sites are summarized in Table 1. These three sites have been chosen to reflect a diversity of health system contexts, to strengthen the generalisability of the study findings and to meet trial recruitment targets within the allocated timeframe.

**Table 1 T1:** The characteristics of the COPSI trial sites.

Site	Tamil Nadu	Goa	Satara
**Collaborators**	Schizophrenia Research Foundation http://www.scarf.org	Consulting Psychiatrists in private sector	Consulting Psychiatrists in private sector and 'Parivartan' and 'Nirmittee'

**Type of service provider**	Non Government Organization (NGO)	Private sector individual practices	Mixed model- combination of private consulting Psychiatrists and NGO's working in tandem

**Catchment area description**	Population coverage of approximately 500,000.	Population coverage of approximately 1 million.	Population coverage of approximately 2.0 million from nearby urban and rural areas
	Participants will be from 235 villages in Kanchepuram district of Tamil Nadu.	Referrals treated from all parts of Goa.	Referrals are from the surrounding urban and rural areas of western Maharashtra
	People with schizophrenia mainly from rural settings.	People with schizophrenia mainly from urban and peri-urban settings.	People with schizophrenia from both rural and urban settings
	Majority belong to lower socioeconomic section of the community.	Predominantly middle and upper socio-economic status population who can afford private care.	Wide range of social classes represented.

**Usually available treatments at facilities**	*Services available:* Out- patient care once every 2 weeks at each of the community clinic centres.	*Services available:* All collaborators are solo practitioners	*Services available:* Out-patient care 6 days a week in designated clinics
	1 Psychiatrist, 1 Psychiatric Social Worker and 1 trained Assistant available at each centre during the clinic.	Out-patient care 6 days a week in designated urban clinics In-patient care provided through liaison with private hospitals	IP care: In multi specialty hospital with registered private psychiatric unit for 20 psychiatric beds.
	*Intervention:* Main treatments are antipsychotic and other psychotropic medications and brief counselling for families and persons with schizophrenia.	*Intervention:* Main treatments used are anti-psychotic and other psychotropic medications with brief advice and counselling for families and persons with schizophrenia.	*Intervention:* Main treatments used are anti-psychotic and other psychotropic medications with brief advice and counselling for families and persons with schizophrenia
	*Description of usual care process:* Consultation lasts for about 20 minutes and usually includes family members.	*Description of usual care process:* Consultations last about 30 minutes and usually include family members.	*Description of usual care process:* Consultations last about 30 minutes and usually include family members.
	*Costs of medicines:* Free medications are given to all persons with schizophrenia attending the community clinics.	*Costs of medicines:* Medicines are purchased from pharmacies entirely through out of pocket expenses	*Costs of medicines* Medicines are purchased from pharmacies entirely through out of pocket expenses

**Whether any community care is already available**	No community care available	No community care available	No community care available

**Number of inpatient beds**	Nil- referrals to existing hospitals when necessary for acute care	On an as needed basis in private hospitals	20

**Average number of total OP attenders/week**	50-60	200	400-500

**Average number of patients/week meeting eligibility criteria**	6-8	5-6	10-12

### Description of the Interventions

#### The collaborative community based care (CCBC) intervention

The CCBC intervention is underpinned by three key principles:

• firstly, the intervention is planned and implemented for each participant in close collaboration between the person with schizophrenia, the primary care giver(s) and the treatment team members (comprising the lay CHW, a supervising Psychiatric Social Worker and the treating Psychiatrist);

• secondly that the intervention is provided in a flexible manner that reflects the unique needs of the person with schizophrenia and their caregivers and;

• thirdly, that the intervention will promote respect, autonomy and dignity for the person with schizophrenia and caregivers.

The inclusion of the specific treatment components within the treatment package have been guided by:

• evidence that the treatment is locally feasible, acceptable and potentially of low cost;

• evidence for the effectiveness of the treatment in low and middle income settings and;

• evidence that it can be delivered by lay health workers

The CCBC intervention will be coordinated and delivered by lay CHWs who have completed at least 10 years of schooling and have been systematically trained at each site over 6 weeks. The training is based on the intervention manual that follows a modular structure covering various aspects of the illness, specific components of the intervention and the operational requirements of the trial related documentation and supervision http://www.sangath.com/details.php?nav_id=60. The CHWs will be closely supervised at each site by Psychiatric Social Workers working as designated Intervention Coordinators. They will coordinate the overall delivery of the intervention and assure the quality and fidelity of the intervention at the site. The treating Psychiatrists will provide clinical leadership for the community care teams and ongoing supervision to maintain safety and quality standards. Overall, the continued supervision of the CHWs through joint onsite visits, weekly group meetings and in scheduled meetings with the Psychiatrist is an essential component of the CCBC intervention.

The treatments included in the intervention package are:

• *structured psycho-educational information *about various issues related to the understanding and proactive management of the illness for the participant and the care givers as well as specific efforts to identify and address experiences of stigma and discrimination

• *adherence management *strategies to reduce the rates of non-adherence to treatments

• *health promotion strategies *to improve the physical health status of people with schizophrenia

• Specific *rehabilitation strategies *to improve the personal, social and vocational functioning of participants

• Linkage to *self help groups *and other methods of user led support

• Developing *networks with community agencies *to address social problems in the family like poverty or interpersonal disputes and facilitate a supportive framework for participants to seek employment and access to social and legal benefits

The intervention is delivered in three phases. In the initial, 3 month *intensive engagement phase*, the key tasks will include developing a positive therapeutic alliance with the person with schizophrenia and care givers, conducting the needs assessment and generating the collaborative individual treatment plan. There will also be a focus on identifying and addressing familial social difficulties that have an adverse impact on the person with schizophrenia, adherence management and structured psycho-education sessions. We anticipate that CHWs will conduct 6-8 home based (or other convenient location nominated by the person and care givers) sessions during this phase.

In the second, *stabilization phase *during months 4-7, the CHWs will conduct a total of 6-8 fortnightly sessions. In this phase, the focus will be on addressing the unmet or partially met needs from the first phase, reinforce psycho-education and adherence, and introduce other components like health promotion, rehabilitation needs assessment and interventions (for example, improving activities of daily living skills and social skills training), and improving social interactions within and outside of the family.

In the final, *maintenance phase *during months 8-12, the CHWs will conduct 6 sessions. In this phase we intend to reinforce the progress made, discuss strategies to deal with distressing symptoms, discuss ways of dealing with experiences of stigma and discrimination, focus on restoration of social and economic roles, generate a relapse prevention plan and address remaining unmet needs, to the extent possible before a carefully planned termination.

In total, we anticipate that each participant in the CCBC arm will receive a maximum of 22 planned contacts during the 12 months of the intervention, and that each CHW will carry a maximum case load of 25 people with schizophrenia at any one time. In evaluating the intervention, we have set an a priori definition of 'minimum adequate' as being 12 sessions of the CCBC sessions delivered over 12 months.

All informational materials meant for the use of participants and caregivers has been systematically translated into the five regional languages used across the trial sites. The intervention has been systematically piloted at each of the sites. Based on the results of the field testing, the final content and process of the phase specific delivery of the intervention has been manualised, as mentioned earlier.

#### Facility based Care (FBC)

'Facility Based Care' is the care usually provided by mental health practitioners for persons with schizophrenia and their families. In two of the sites i.e. Goa and Satara, Psychiatrists in the private sector are the primary care providers with trained assistants recording essential socio demographic details in some of these clinics. In rural Tamil Nadu, a team of three persons are involved in the clinics. A trained assistant records essential socio demographic details of all persons who come to the clinic. A brief clinical history is then elicited by the Psychiatric Social worker (PSW) who then presents the findings to the clinic Psychiatrist for detailed assessment and treatment planning. In Goa and in Satara, the Psychiatrists are the first point of contact and, for the most part, conduct all necessary procedures themselves. Across all settings, consultations last from 15-45 minutes; persons with schizophrenia presenting for the first time are reviewed once or twice a month while those who are clinically stable are reviewed more flexibly- once a month- 3 months. Almost all persons with schizophrenia in these facilities are prescribed psychotropic medications with the newer antipsychotic medications being preferred (as in India, these newer drugs are cost comparable with the older antipsychotic drugs) while the use of antidepressants, anticholinergic, sedatives and modified Electroconvulsive treatment (ECT) is based on individual clinical needs. All psychiatrists also provide specific information about the illness, encourage adherence and discuss other specific concerns that the person with schizophrenia or their family members have; all of these are provided on an 'as needed' basis. The salient difference between the two arms is that in the CCBC arm, a complex psychosocial intervention, tailored towards individual needs, will be delivered in an accessible (home based) and structured manner by a dedicated CHW. There will be no guidelines or protocols made available to Psychiatrists for the medical treatment of participants as this is more representative of usual care in India. FBC will continue to be available to participants in both study arms and treating Psychiatrists will be unblinded while providing care for participants.

### Selection of participants

COPSI is an effectiveness trial and to improve the generalisability of the study results, we will:

• recruit persons with schizophrenia into the trial from those who present to routine, 'real life' treatment settings and

• include those persons with schizophrenia for whom community based care is justified even in low resource countries.

Thus, the inclusion criteria for participating in the trial are:

• Trial participants must be between the ages of 16-60 years

• Have a primary diagnosis of schizophrenia as per ICD-10 DCR criteria [11]

• Have had an illness duration of at least 12 months and an overall moderate severity of the illness based on the Clinical Global Impression-Schizophrenia(CGI-SCH) scale [12] rating. This reflects the threshold at which additional community care is warranted in resource constrained settings where community based care can realistically be offered only for those with high needs.

• Be residing within the study catchment area for the next 12 months.

In the Tamil Nadu site, participants will be selected from those identified through a community survey in the study area and will then be referred to community clinics for assessment by the Psychiatrists. In Goa and Satara, participants will be approached for recruitment from the clinical practices of the collaborating Psychiatrists. In these settings, we anticipate two pathways for recruitment: (a) people with schizophrenia from within the existing caseloads at each of the sites who meet inclusion criteria; and (b) people with schizophrenia who have presented for care for the first time and meet all inclusion criteria.

### The flow of participants in the trial

The collaborating Psychiatrists will identify all persons with a primary diagnosis of ICD 10-DCR schizophrenia in their setting by using a checklist. All persons with schizophrenia will be assigned a unique identification number and the Psychiatrist will fill out an initial screening form to confirm eligibility and record other basic socio-demographic and clinical details. From this 'universe' of persons with schizophrenia, for those who meet all inclusion criteria, the Psychiatrists will provide a brief overview of the trial together with a standard flier outlining the purpose of the trial (that is translated to all relevant local languages) and ask the person and the caregiver (s) whether they are interested in participating in the trial. If the person or the caregiver does not agree to proceed further, the Psychiatrist will briefly record their reasons for their not agreeing, whenever possible. For those who have refused, the Psychiatrist has the option of revisiting their participation during the course of the recruitment period. If both are interested to continue, the Psychiatrist will then fill out additional clinical details and take written (for non literate persons, their left thumb impression will be taken) assent for the independent consent procedure.

Subsequently, an independent, trained researcher will conduct the informed consent interview. The consent procedure has been specially designed to provide adequate information about the trial in a manner that is matched to the literacy levels of the participant and caregiver and to minimize the cognitive difficulties that persons with schizophrenia commonly face in processing information for making an informed decision[13]. After the procedure, the participant and the caregivers make an informed choice to participate or not. At this stage, the researcher will record the reasons for participation or refusal, whenever possible. Once informed consent has been obtained, trained researchers will complete the baseline quantitative assessments for both the participant and the caregiver(s) who are then assigned a unique trial ID.

From this overall sample of participants, a purposively selected sub sample of 12 participant and their caregivers will be chosen at each of the three sites for the additional baseline qualitative interviews. Once all baseline assessments have been completed, participants will be randomly assigned to either of the 2 arms of the study for the next 12 months.

The identification, registration and subsequent flow of participants in the trial will be governed by the trial standard operational protocol (SOP) at all sites. This will be monitored closely using a set of process indicators and any deviations from the protocol and the reasons for the same will be carefully recorded. The flow of participants during the conduct of the trial, illustrated in Figure 1, will be monitored and reported in compliance with the recent CONSORT recommendations[14].

**Figure 1 F1:**
[figure not shown]
Flow of participants during the conduct of the trial

### Randomisation

#### Generating the allocation list

Three lists have been generated independently by the Trial Statistician in London, one for each site, and transmitted to the site Data Managers prior to the commencement of the recruitment for the trial. The pre determined allocation sequence cannot be altered during the recruitment of participants in the trial.

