#### Allocation concealment

The site Data Managers will be entrusted with keeping the allocation list secure (through password protected files). The matching of the study numbers of the recruited participants with their randomization numbers and the concealment of randomization from interviewers will also be managed by the central Data Manager to ensure that no one has access to the allocation list.

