#### Implementation

For logistic reasons, the site Data Managers will be responsible for assigning the unique trial ID for each randomized participant in the trial; if the participant is assigned to the CCBC arm, the Data Manager will notify the site intervention coordinator and pass on the required contact information. For participants in both arms, the Data Manager will also ensure that treating Psychiatrists are provided with the specially designed clinical booklet to record treatment details for the next 12 months.

For statistical reasons (see 'sample size estimation' below) there will be unequal allocation, with a larger number in the intervention arm. The rationale for the unequal randomization is the additional source of variability in the intervention arm - the effect of individual community health workers which is built into the analysis and allowed for in the sample size as recommended in the recent CONSORT guidelines for non pharmacological trial design and reporting[15]. It is difficult to precisely estimate the magnitude of this extra variability (the intra-class correlation), but the value chosen for the intervention arm of 0.1 is conservative: a recent review of a large number of primary care variables found the inter-quartile range to be 0 to 0.032[16]. For practical reasons, the ratio of numbers in the two arms was fixed at a whole number; for the study this has been chosen to be 2:1. The method of allocation will be through the use of permuted blocks, with random block sizes chosen from 3, 6 and 9 using the '*ralloc*' routine in Stata.

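### Each site's Data Manager holds the complete allocation sequence before recruitment, which contradicts the claim that no one has access and creates an avoidable risk of foreknowledge

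*Protocol article*

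**What the plan says.** Four places in the protocol article bear on this.

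- *Generating the allocation list* tells us where the sequences come from and go to: "Three lists have been generated independently by the Trial Statistician in London, one for each site, and transmitted to the site Data Managers". The transfer takes place "prior to the commencement of the recruitment for the trial". The section also states that the order is fixed in advance and cannot be changed while participants are being recruited.
- *Allocation concealment* names the custodian: "The site Data Managers will be entrusted with keeping the allocation list secure (through password protected files". It then turns to matching study numbers with randomisation numbers and to keeping interviewers unaware. These tasks, it says, will "also be managed by the central Data Manager to ensure that no one has access to the allocation list".
- Under *Implementation*, on grounds of logistics, "the site Data Managers will be responsible for assigning the unique trial ID for each randomized participant in the trial". The Data Manager also tells the site intervention coordinator who has been allocated to CCBC. Allocation is 2:1 in permuted blocks, with sizes drawn at random from 3, 6 and 9.
- *Ethical considerations*: a Data Manager, not specified as site or central, checks each participant's baseline data, strips the identifiers and assigns the trial ID.

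*The flow of participants in the trial* sets the order of events: psychiatrists screen and invite, an independent researcher takes consent, researchers complete the baseline assessment, and only then is the participant randomised.

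**The concern.** A password keeps other people out of a file. It does not conceal the list from the person who holds the password, and here that person is on site and handles new participants. The assurance that no one has access is therefore untrue as written. A reader also cannot tell whether the site or the centre links a participant to the next place on the list.

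This matters because participants, caregivers and treating psychiatrists all know the allocation once it is made. Masking of the outcome assessors protects measurement, but it does not protect the make-up of the arms. That depends on nobody being able to influence entry, or the order of entry, with the next assignment in view.

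**Working it through.** The protocol gives no figure on this point, so the check is mainly a comparison of statements.

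**1. Who holds the list?** *Generating the allocation list* and the first sentence of *Allocation concealment* both say the site Data Managers. The second sentence of *Allocation concealment* says arrangements ensure that nobody has access. Both cannot be true.

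**2. Who makes the assignment?** *Allocation concealment* gives the matching to the central Data Manager. *Implementation* gives trial IDs for randomised participants, and notification of CCBC allocations, to the site Data Managers. The word *also* in "concealment of randomization from interviewers will also be managed by the central Data Manager" could mean that the two roles share the task. Neither section says so.

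**3. When is the trial ID given?** *The flow of participants in the trial* places it after baseline assessment and before randomisation is described. *Implementation* ties it to participants already randomised. If the ID fixes a participant's place on the list, this order matters.

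**4. Does the fixed sequence close the gap?** No. It stops the list being changed. It does not fix the order in which waiting participants are matched to it. Table 1 expects 6-8, 5-6 and 10-12 eligible patients a week at the three sites, so more than one could be waiting at the same time.

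**5. Do random block sizes close the gap?** They protect only against people without the list. Illustration, assuming sizes 3, 6 and 9 are equally likely and 94 participants per site (282 / 3; the protocol says the true split is slightly unequal):

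- Knows only the 2:1 ratio and always guesses CCBC: right 2/3 = 67% of the time.
- Has no list but knows every past assignment and each block's size: right about 74% of the time by simulation, with about 27% of assignments certain in advance.
- Holds the list: right 100% of the time.

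Hand check on a block of 3, whose possible orders are CCF, CFC and FCC (C for CCBC, F for FBC). Guessing the arm with more places left, and CCBC when tied, gives 3 + 2 + 2 = 7 right out of 9 (78%). The certain assignments number 1 + 1 + 2 = 4 out of 9 (44%). Longer blocks are harder to predict, which is why the overall figures are lower.

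**The case against.** The strongest reply is that concealment protects against foreknowledge by those who decide who enters, and the Data Manager is not described as one of them. No section gives the list to the psychiatrists who screen or to the researchers who take consent, and randomisation follows both consent and baseline. The claim that no one has access stands in a sentence about interviewers and may be loose wording for no one else. A standard operational protocol, not shown, governs registration and flow and may contain the release steps.

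Much of this stands, and it limits the point to a risk. It does not remove the contradiction: an unseen procedure cannot make a list held on site into one that nobody can access.

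Three stronger readings should be resisted.

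- A reader might infer that psychiatrists can steer entry, because for people who refuse "the Psychiatrist has the option of revisiting their participation during the course of the recruitment period". That route needs the psychiatrist to know the next assignment, and nothing says so. The documents also offer no evidence that families prefer one arm.
- A reader might put a size on the bias by multiplying a share of steered entries by a prognostic gap. Neither input is in the documents. Any such product would in any case have to be set against the 13-point PANSS target in *Sample size estimation*, and not only the smallest scenario there, 7.2 points.
- A reader might argue that a pre-post correlation of 0.4 explains only 0.4² = 16% of variance, so most of any bias would survive adjustment. That figure describes outcome variance, not the share of selection bias that remains. Selection on visible severity would act largely through baseline PANSS, which the analysis adjusts for. Selection on unmeasured prognosis would not be removed.

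**Conclusion.** The concern holds as an internal contradiction together with an avoidable weakness in allocation concealment. On the protocol's own account, the full sequence for each site sits with a local staff member before the first participant is recruited, that person handles allocation tasks, and the assurance of no access is wrong as written. The sections also disagree on whether the site or the centre makes the assignment.

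In size, the list holder can foresee all upcoming assignments, against about 67% from the ratio alone. The effect on the treatment comparison cannot be derived from the documents and could be nil. Bias would need misuse by the list holder or a leak to someone who recruits, and neither is shown. The documents do not support saying that concealment was broken.

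The conclusion rests on reading *Implementation* as placing allocation tasks with the site. It does not depend on the unspecified Data Manager in *Ethical considerations* being the site one. If so, the same person would also see baseline data before the link is made, which would strengthen the case for change. The procedure should be changed; the sample size and the analysis are not affected.

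**What to change.** - The Trial Statistician and the central Data Manager alone hold the three lists.
- The site registers each participant once consent and baseline assessment are complete. The centre logs that entry irrevocably with a time, and then releases that single allocation to the site Data Manager, who carries out the notifications already described.
- The lists have already been sent out, so withdrawing them does not undo what is known. Regenerate every unused part, or the whole lists if recruitment has not begun.
- Rewrite *Generating the allocation list*, *Allocation concealment* and *Implementation* as this one procedure. State truthfully who has access, and say whether the trial ID is given before or at randomisation.

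The cost is one message per participant (282 in all), a short wait for each allocation, and the new sequences. The article already names a central Data Manager, so no new post is implied, but the logistic reasons for local handling would need to be met by prompt central replies. Cutting a block part-way disturbs the 2:1 balance only slightly. The worst case in a block of 9 is six CCBC places used in a row, against 6 × 2/3 = 4 expected, a difference of 2 participants at that site.
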